# High-definition transcranial direct current stimulation (HD-tDCS) in major depressive disorder with anxious distress—a study protocol for a double-blinded randomized sham-controlled trial

**DOI:** 10.1186/s13063-024-08157-y

**Published:** 2024-05-15

**Keywords:** High-definition transcranial direct current stimulation, Augmentation therapy, Major depressive disorder, Anxious distress specifier

## Abstract

**Background:**

Comorbid anxiety disorders and anxious distress are highly prevalent among individuals with major depressive disorder (MDD). The presence of the DSM-5 anxious distress specifier (ADS) has been associated with worse treatment outcomes and chronic disease course. Few studies have evaluated the therapeutic effects of High-definition transcranial direct current stimulation (HD-tDCS) on depressive and anxiety symptoms among MDD patients with ADS. The current randomized controlled trial aims to assess the efficacy of HD-tDCS as an augmentation therapy with antidepressants compared to sham-control in subjects of MDD with ADS.

**Methods:**

MDD patients with ADS will be recruited and randomly assigned to the active HD-tDCS or sham HD-tDCS group. In both groups, patients will receive the active or sham intervention in addition to their pre-existing antidepressant therapy, for 2 weeks with 5 sessions per week, each lasting 30 min. The primary outcome measures will be the change of depressive symptoms, clinical response, and the remission rate as measured with the 17-item Hamilton Depression Rating Scale (HDRS-17) before and after the intervention and at the 2nd and 6th week after the completed intervention. Secondary outcome measures include anxiety symptoms, cognitive symptoms, disability assessment, and adverse effects.

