### Trial design

The study described in this protocol is a RCT to evaluate the superiority of an active HD-tDCS program for MDD patients with ADS compared with the sham HD-tDCS program. MDD patients with ADS will undergo at least 2 weeks of maintenance pharmacotherapy prior to stimulation initiation and continue such treatment throughout the entire stimulation period. Fifty-eight MDD patients with ADS will be randomized (1:1) in the active HD-tDCS group or the sham HD-tDCS group.

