### Primary outcome

The primary outcome will be the change of depressive symptoms. The clinical response rate and remission rate, as assessed by the HDRS-17 (17-item Hamilton Depression Rating Scale) at 6 weeks post-intervention were measured. The Chinese version of HDRS-17 has been validated for its psychometric properties and is commonly used to evaluate depressive severity in Chinese patients with depression symptoms [18]. The clinical response is defined as a ≥ 50% reduction from the baseline [19], and a score of 7 or less will be used as an indicator of remission [20].

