### Statistical analysis

Continuous variables will be summarized using the mean and standard deviation measures. Categorical variables will be presented in terms of frequency and percentage. Between-group comparisons will be assessed using the Mann–Whitney *U* test for continuous variables and either the chi-square test or Fisher exact test for categorical variables. The primary outcome will be analyzed based on the intention-to-treat principle, with worst case imputation applied. For repeated continuous outcomes, a mixed linear model will be employed, which includes the interaction between group (active versus sham) and time (baseline, post-assessment, 2-week and 6-week follow-up assessment.

The hypotheses will be tested using unpaired, two-tailed tests at a significance level of 0.05. The software SAS, v.9.4 (SAS Institute Inc.), was utilized.

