## Discussion

In the DSM-5, an ADS has been included for the diagnosis of MDD [30], which is common among MDD patients without comorbid anxiety disorders and correlated with some of their sociodemographic and clinical characteristics [4]. It captures the core symptoms of anxious emotions and cognitions, providing a valuable framework for treatment planning and symptom assessment [4]. The ADS predicts poorer treatment outcomes as shown by higher depression severity, lower remission rates, and greater frequency of antidepressant side effects in patients with MDD on adequate antidepressant treatment; in contrast, the presence of comorbid anxiety disorders did not predict these treatment outcomes [4]. The assessment of anxiety distress according to DSM-5 was found to be significant not only during the acute phase but also in the continuation/maintenance phase of MDD [31]. This simple 5-item specifier holds great potential for clinical utility in the planning and monitoring of treatment for depressed patients; therefore, new and effective interventions beyond pharmacotherapy and psychotherapy are imperative for this subpopulation with heightened illness-associated burden and risks [6].

This randomized controlled trial aims to evaluate the effectiveness of HD-tDCS as augmentation therapy with antidepressants in ameliorating depressive symptoms in MDD patients with ADS. To this aim, the trial compares the effect of HD-tDCS and sham-control HD-tDCS on improving depressive symptoms in addition to the pre-existing antidepressant regimen. The operationalization of depressive symptoms encompasses three levels, specifically the change in depressive symptoms, clinical response, and remission rate as assessed by HDRS-17. The secondary objectives of this study are to evaluate the impact of the intervention on anxiety symptoms, cognitive function, disability resulting from mental disorders, and adverse effects upon completion of the intervention. We also plan to detect any sustained effect by checking the changes at the 2nd week and 6th week after the finished intervention.

The findings of this trial will prove valuable in the management of MDD patients with ADS, as a new safe treatment option is required to alleviate depressive symptoms for those exhibiting inadequate responses to conventional antidepressants. HD-tDCS is anticipated to be efficacious in ameliorating cognitive function and daily functioning, which are frequently compromised in individuals with MDD.

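### The primary outcome is defined inconsistently: three co-listed HDRS-17 measures over all visits in the abstract, change alone with no clear visit in the outcomes section, and no primary contrast in the analysis

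*Protocol article*

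**What the plan says.** All places are in the protocol article.

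- **Abstract, Methods.** "The primary outcome measures will be the change of depressive symptoms, clinical response, and the remission rate". The sentence goes on to give the times: "before and after the intervention and at the 2nd and 6th week after the completed intervention". No measure and no visit is ranked above the others.
- **Outcomes, Primary outcome.** It opens in the singular: "The primary outcome will be the change of depressive symptoms". A separate sentence under the same heading then covers response and remission, which are tied to HDRS-17 "at 6 weeks post-intervention were measured". Grammatically, the 6-week time belongs to response and remission and not to change.
- **Table 1.** HDRS-17 is listed under the primary outcome at screening and at T0 to T3.
- **Statistical analysis.** Repeated continuous outcomes go to a mixed linear model with a group-by-time interaction over four time points. Categorical variables go to a chi-square or Fisher exact test. "The hypotheses will be tested using unpaired, two-tailed tests at a significance level of 0.05".
- **Sample size calculation.** One continuous effect (Hedges' g = 0.743) at 80% power and 5% alpha: 24 per arm, 29 after allowing for dropout.
- **Discussion.** "The operationalization of depressive symptoms encompasses three levels, specifically the change in depressive symptoms, clinical response, and remission rate as assessed by HDRS-17". Later: "We also plan to detect any sustained effect by checking the changes at the 2nd week and 6th week after the finished intervention".

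**The concern.** A confirmatory trial needs one answer, fixed beforehand, to the question of which result decides it. Here the abstract offers three measures at three post-baseline visits, the outcomes section offers one measure without a clear visit plus two at week 6, and the model produces a multi-visit interaction with no contrast singled out. Someone reporting the trial could point to text supporting change at end of treatment, change at week 6, the overall interaction, response, or remission.

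Two things are at stake. The first is the error rate: the sample size assumes a single comparison at 5%, and that holds only if a single comparison decides the trial. The second is the question itself. Background medication is to "continue such treatment throughout the entire stimulation period", which covers T1 but not the two follow-up visits. A difference at the end of the sessions and a difference six weeks later are therefore different quantities. That is a reason to state the visit; it has no bearing on type I error.

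**Working it through.** **1. The plan's own figure.** Two-sample t test, d = 0.743, 24 per arm, noncentral t. One-sided 5% gives 81% power; 23 per arm gives 79.8%, so 24 is the smallest size and the stated 48 is reproduced. Two-sided, 24 per arm gives 71% and 30 per arm are needed. The sidedness is a separate matter. What counts here is that either calculation is for one continuous comparison at the full 5%, with nothing for response or remission and no division of alpha.

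**2. The passages side by side.**

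| Place | Primary measure(s) | Visit |
|---|---|---|
| Abstract | change, response, remission | post, week 2, week 6 |
| Primary outcome | change (singular); response and remission added beneath | week 6 for response and remission; none clearly for change |
| Statistical analysis | not specified | four time points, no primary contrast |
| Sample size | one continuous difference | none |

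The abstract and the Primary outcome section cannot both be followed.

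**3. Bound with independent tests.** Chance of at least one false positive among k tests = 1 − 0.95^k.
- k = 3: 1 − 0.857 = 14.3%
- k = 9: 1 − 0.630 = 37.0%

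The measures all come from one scale and are correlated, so the true values are lower.

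**4. Simulation with correlated scores and no treatment effect.** From the document: 29 per arm, response as a reduction of at least 50%, remission as a score of 7 or less, and baseline of at least 8. Assumed, because the document gives none of it: baseline mean 22 (SD 5); follow-up means 14/13/12 or 11/10/9 (SD 6); correlation with baseline 0.4; correlation between follow-up visits 0.5 to 0.85; no dropout; 20,000 trials per setting. These give null response rates of 31–66% and remission rates of 14–40%. Success means any listed test with p < 0.05. The group-by-time test is the multivariate equivalent of the interaction in an unstructured mixed model.

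| Tests counted as primary | chi-square | Fisher exact |
|---|---|---|
| Change at week 6 (Mann–Whitney) + week-6 response and remission | about 11% | about 8% |
| Group-by-time test for change + week-6 response and remission | 11–12% | 8–9% |
| Group-by-time test for change + response and remission at all three visits | 21–25% | 13–15% |
| All three measures at each of three visits (nine tests) | 22–29% | 15–20% |
| All three measures required at week 6 | below 1% | below 1% |

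Treating 20% of patients as dropouts with no change and no response, in the chi-square version, leaves the first row at about 11% and the nine-test row at 23–28%.

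**5. After the fix.** One measure at one visit, tested at 0.05, has an error rate of 5%. Keeping three co-primary measures at one visit with Bonferroni would mean testing each at 0.05/3 = 0.0167. For g = 0.743, the normal approximation gives n per arm = 2 × (2.394 + 0.842)² / 0.743² ≈ 38, or 76 in total before dropout, against the 48 stated.

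**The case against.** The best defence is that the protocol does have a single primary outcome. The Primary outcome section opens in the singular with change, the objectives concern depressive symptoms, and the sample size rests on one continuous effect. On that reading, response and remission are descriptive companions and week 6 is the named visit. This is a fair reading and probably the easiest to adopt. It does not remove the conflict: the abstract plainly lists three primary measures, and the week-6 time is not clearly attached to change.

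Several stronger readings are tempting, and the document does not support them.

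- *The primary visit is stated in three different ways.* Only the Primary outcome section ties a single visit to primary measures. The Discussion's remark about sustained effect at weeks 2 and 6 at most hints at end of treatment as the main time, and is compatible with week 6 as primary. The Discussion also speaks of three levels without calling them primary.
- *There are nine primary tests and an error rate of about a quarter.* No passage says that one significant result suffices. The nine-test figure also runs a separate test of change at each visit, whereas the analysis section gives repeated continuous outcomes a mixed model. That case is conditional.
- *The absence of a multiplicity procedure is itself an error.* A hierarchy or adjustment may sit in an analysis plan that is not shown. The finding is the contradiction over the primary outcome, which the protocol itself has to settle.
- *Response and remission have a known power shortfall.* The document gives no expected rates, so any power figure for them would rest wholly on assumption.
- *End of treatment is the correct primary visit.* The medication commitment makes the visits differ in meaning, but week 6 is the only visit the Primary outcome section names. The article also criticises its pilot for short duration.

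**Conclusion.** The point stands as an inconsistency in the text with a conditional consequence. The abstract and the Primary outcome section disagree on how many primary measures there are. Change has no clear primary visit, and the analysis names no primary contrast, while the sample size assumes one comparison at 5%.

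If any one significant primary test were taken as success, the false-positive rate would be about 8–12% for change together with week-6 response and remission. It would be about 15–29% if all three visits were also tested separately. The spread reflects chi-square against Fisher, Mann–Whitney against the group-by-time test in the week-6 case, and the assumed score distributions and correlations. None of these inputs except the definitions and the 29 per arm comes from the document, so the figures show direction and rough size only. The one reading below 5% requires all three measures to be significant, and no passage states it.

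This should be settled before unblinding, because the headline conclusion depends on it.

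**What to change.** Before unblinding, name one primary outcome: the between-group difference in HDRS-17 change from T0 at one stated visit, estimated as that visit's contrast from the mixed model and tested two-sided at 0.05. The choice of visit is the sponsor's; week 6 is the only one the Primary outcome section names. Make response, remission and the remaining visits secondary, and test them in a fixed order after the primary if claims are wanted from them. Use identical wording in the abstract, outcomes, analysis, discussion and registry record.

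The cost is that two of the three measures lose the label of primary. The amendment section lists changes to outcomes and analyses as significant, so ethics approval and a registry update are needed. No extra patients or visits are required by this change.

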**Discussion:**

The HD-tDCS applied in this trial may have treatment effects on MDD with ADS and have minimal side effects.

**Trial registration:**

The trial protocol is registered with www.chictr.org.cn under protocol registration number ChiCTR2300071726. Registered 23 May 2023.

**Supplementary Information:**

The online version contains supplementary material available at 10.1186/s13063-024-08157-y.

## Introduction

### Major depressive disorder with anxious distress exerts a significant impact on the healthcare system

To emphasize the importance and impact of the concurrence of anxiety and depressive disorders, the Diagnostic and Statistical Manual of Mental Disorders-5th edition (DSM-5) has added the anxious distress specifier (ADS) [1]. The diagnostic criteria for ADS require the presence of at least two of the following symptoms: (1) feeling keyed up or tense, (2) restlessness, (3) difficulty concentrating due to worry, (4) feeling that something awful may happen, and (5) feeling that one may lose control of oneself. Data suggests that ADS criteria are met by 50–65% of individuals diagnosed with major depressive disorder (MDD), and the specifier is more effective than comorbid anxiety diagnoses in predicting significant clinical outcomes such as chronicity, remission, and disability [2–5]. This underscores its presumed clinical relevance. Greater severity of illness was observed 

in adults with ADS, as evidenced by a higher frequency of hospitalizations, increased rates of suicidal ideation, greater severity of depressive symptoms, more significant workplace impairment, reduced quality of life, and self-reported cognitive decline [6]. Therefore, there is an urgent need for a novel treatment option that can effectively and tolerably address the needs of these subjects.

### Advantages of a new format of tDCS: HD-tDCS

A main drawback of traditional transcranial direct current stimulation (tDCS) is the spatial crudity of its effect. The highest cortical current density may not occur directly under the target electrode [7], which probably alters the effects of tDCS and contributes to the inconsistent results of existing tDCS studies [8, 9]. HD-tDCS was developed as a solution to tackle this issue with high precision and accuracy. Similar to conventional tDCS, which utilizes an anode and a cathode placed on the scalp to establish a unidirectional current flow, HD-tDCS also involves the use of both anode and cathode electrodes, typically consisting of more than two smaller electrodes. In the latter, precise delivery of current to the intended target site is its primary advantage. Although various montages can be explored, the “4X1 ring” montage is by far the most commonly used. It utilizes a center anode electrode surrounded by four return cathode electrodes and confers HD-tDCS with the ability to achieve a single desired activity without inducing cortical stimulation due to opposite polarity [10, 11]. The density of the cortical field and spatial focality can be modulated by changing the diameter of the ring of electrodes [12]. In addition to enhancing the spatial focality of stimulation, the augmented effects of neuroplasticity may also manifest in longer-lasting after-effects, as demonstrated in a previous study on HD-tDCS [10]. At the same time, the tolerability was found to be comparable to that of conventional tDCS [13]. No HD-tDCS study of MDD with ADS has yet been performed. Therefore, our team conducted a pilot study to test the effects and tolerability of HD-tDCS on MDD patients with ADS [14].

### Results from our pilot study

A pilot study [14] was conducted by our team in 39 adults who have MDD with ADS received five consecutive daily sessions of 20-min active or sham HD-tDCS interventions weekly for 2 weeks. The results revealed that the HD-tDCS has significant efficacy in the treatment among MDD patients with anxious distress. The rate of adverse events(e.g., itching, tingling and headache) showed no significant differences between the two groups. Additionally, no severe adverse events or mania was reported. Nevertheless, it should be noted that the trial was of short duration, limited to hospitalized patients, and did not include an evaluation of cognitive or daily functioning. A double-blinded randomized controlled trial (RCT) with an adequate sample size and adequate study periods is warranted to confirm the efficacy of HD-tDCS as an augmentation therapy with antidepressants in MDD patients with ADS.

### Objectives

This study proposes a RCT with parallel group design, in which participants are randomly allocated to the experimental group or the sham group in a 1:1 ratio. This trial intends to investigate the superiority of HD-tDCS treatment over sham stimulation. It is hypothesized that MDD patients with ADS receiving ten consecutive sessions of HD-tDCS will report a positive effect on the impact of on depressive symptom and confirm the findings of our pilot investigation, compared to patients receiving sham stimulation.

### Ethics and dissemination

The study is being conducted in accordance with the Declaration of Helsinki and was approved by the local ethics committee of Zhenjiang Mental Health Center (ethics approval number: 2023Y01) on April 26, 2023; then, the ethics committee’s phone, email, and address are as follows: [name], [contact], and [name]. Investigators will obtain signed informed consent forms from participants prior to their enrollment in the study. Following the study, all patients will continue to receive ongoing medical care from the investigators. The findings of this research will be disseminated through scholarly articles and presentations at national and international conferences. Therefore, this study will make a valuable contribution to the current treatment options for patients with MDD and offer a non-pharmacological intervention approach that will be readily available in the near future.

### Trial design

The study described in this protocol is a RCT to evaluate the superiority of an active HD-tDCS program for MDD patients with ADS compared with the sham HD-tDCS program. MDD patients with ADS will undergo at least 2 weeks of maintenance pharmacotherapy prior to stimulation initiation and continue such treatment throughout the entire stimulation period. Fifty-eight MDD patients with ADS will be randomized (1:1) in the active HD-tDCS group or the sham HD-tDCS group.

## Methods

### Recruitment

We will approach patients in the Zhenjiang Mental Health Center outpatient and inpatient units. Our inpatient and outpatient care units follow up at least 5000 patients with MDD each year. We will ensure the completion of the study schedule in accordance with the current protocol. Standard clinical care will continue to be provided to all participants upon completion of the trial at our healthcare facility. Recruitment, pre-participation screening, allocation, intervention, and data collection will be conducted between Jun 2023 and November 2025. Our plan is to conclude the study by the end of 2026 and make the results available for analysis. The current study protocol adheres to the SPIRIT 2013 recommendations (Standard Protocol Items: Recommendations for International Trials) [15]. Figure 1 shows the schedule of enrollment, interventions, and assessments.

**Fig. 1 Fig1:**
[figure not shown]
Flowchart of the current study

### Eligibility criteria

The inclusion criteria are as follows:Ability and willingness to provide written informed consent for trial participation and undergo all necessary procedures is required;The age range is between 18 and 65 years old;A diagnosis of MDD with ADS according to the Diagnostic and Statistical Manual of Mental Disorders, Fifth Edition (DSM-5), which is assessed by at least one professional psychiatrist; the presence of specifier was evaluated based on DSM-5 criteria, which mandates that MDD patients exhibit at least two out of five symptoms;Han ethnicity;Right-handedness;Adequate auditory and visual acuity to perform requisite inspections;Presence of depressive symptoms ranging from mild to severe, as measured and defined by HDRS-17 scores ≥ 8 and ≤ 52 [16];Willing to remain on maintenance pharmacotherapy for at least 2 weeks before the stimulation initiation and during the total stimulation period.

The exclusion criteria are as follows:The presence of severe systemic illnesses, including but not limited to severe hepatic, renal, endocrine, cardiovascular, respiratory, hematological, or oncological diseases that are deemed by the investigator as unsuitable for participation in the trial;Any laboratory examination that shows clinically significant abnormalities and may have an impact on the health of participants, as determined by the investigator;A history of any significant medical illness, such as neurological disorders (e.g., cerebral trauma, seizure disorder, etc.), that would render the participant unsafe for trial participation in the investigator’s opinion;Known to have current psychosis as determined by the DSM-5 criteria or a history of a non-mood psychotic disorder;Current substance abuse, including alcohol and/or illicit or prescription drugs;Current or planned pregnancy and/or lactation during the trial;A scalp with abnormal conditions, such as open wounds;A score = 4 for item 3 (suicide) on the HDRS-17;Having undergone or currently undergoing modified electroconvulsive therapy (MECT) or repetitive transcranial magnetic stimulation (rTMS) within the past month;Concurrent participation in another clinical trial or participation within 1 month prior to randomization is not allowed.

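### Remission (HDRS-17 of 7 or less) depends strongly on an entry score that may be as low as 8, yet the stated test for categorical outcomes ignores baseline, which costs power in arms of 29

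*Protocol article*

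**What the plan says.** The Eligibility criteria section of the protocol article admits patients with "HDRS-17 scores ≥ 8 and ≤ 52". The Primary outcome section defines both binary outcomes on the same scale: "The clinical response is defined as a ≥ 50% reduction from the baseline", and "a score of 7 or less will be used as an indicator of remission". Remission carries no minimum change and no minimum baseline. The time point is given as "at 6 weeks post-intervention were measured".

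The status of remission is not uniform. The abstract states: "The primary outcome measures will be the change of depressive symptoms, clinical response, and the remission rate". The Discussion also treats change, response and remission as three levels of the depressive-symptom outcome. The Primary outcome section opens with "The primary outcome will be the change of depressive symptoms" and then covers response and remission under the same heading.

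The Statistical analysis section compares groups by "either the chi-square test or Fisher exact test for categorical variables". Baseline enters only through another route: "For repeated continuous outcomes, a mixed linear model will be employed", with baseline as one of the time levels. The section on randomization describes 1:1 allocation and mentions no stratification by severity.

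**The concern.** A fixed cut at 7, combined with entry from 8 upward, makes remission a very different hurdle for different patients. Baseline HDRS-17 is therefore likely to be the strongest single predictor of remission. A two-by-two test discards that information, so a patient who goes from 8 to 7 counts the same as one who goes from 30 to 7.

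Two things are at stake. The first is power: leaving out a strong prognostic covariate wastes information, and a trial of 58 has little to spare. The second is exposure to chance imbalance. If a few more of the mildest patients fall into one arm, the observed remission rates shift, and the stated analysis has no means of correcting for it. Because remission is listed with the primary outcome in two places, readers will give it weight.

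**Working it through.** The plan gives no figure of its own on this point, so there is none to reproduce. Step 1 needs only the protocol. Steps 2 to 5 rest on assumptions, because the documents give no HDRS-17 mean, SD or retest error.

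**Step 1. The two definitions, baseline by baseline.** Points needed to remit = baseline − 7. Points needed to respond = half the baseline, rounded up.

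| Baseline | Fall to remit | As % of baseline | Fall to respond |
|---|---|---|---|
| 8 | 1 | 12.5 | 4 |
| 10 | 3 | 30.0 | 5 |
| 13 | 6 | 46.2 | 7 |
| 14 | 7 | 50.0 | 7 |
| 20 | 13 | 65.0 | 10 |

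From 8 to 13, remission is possible without response. From 14 upward, remission implies response.

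**Step 2. Dependence on baseline with no true change.** Assume normal retest error with SD s = 2, 3 or 4 points and a continuity correction: P(score ≤ 7) = Φ((7.5 − b)/s).
- b = 8: 0.40, 0.43, 0.45
- b = 12: 0.01, 0.07, 0.13
- b = 20: at most 0.001

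The chance of meeting the response criterion from 8 is Φ((4.5 − 8)/s) = 0.04, 0.12, 0.19.

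**Step 3. Chance imbalance.** Assume that 7% or 16% of patients enter at 8 to 10. With two independent binomial counts of size 29, the arms differ by 3 or more such patients with probability 0.19 or 0.37.

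**Step 4. Does a mild baseline shrink the arm difference?** Assume a common improvement of 3 points, a further 4 points on active treatment, and an SD of change of 5. Sham remission = Φ((7.5 − (b − 3))/5); active remission = Φ((7.5 − (b − 7))/5).

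| Baseline | Sham | Active | Difference |
|---|---|---|---|
| 8 | 0.69 | 0.90 | 0.21 |
| 12 | 0.38 | 0.69 | 0.31 |
| 14 | 0.24 | 0.54 | 0.30 |
| 17 | 0.10 | 0.31 | 0.21 |
| 20 | 0.03 | 0.14 | 0.11 |

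The difference at 8 equals that at 17 and is about twice that at 20. On these inputs, mild entrants do not dilute the comparison.

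**Step 5. Adjusted against unadjusted test.** Simulated trials with 29 per arm, no dropout, baseline normal with SD 6 truncated at 8 and mean 14 or 18, and the changes of step 4. Two-sided 5% tests.

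| Test of remission | Type I error (mean 14; 18) | Power (mean 14; 18) |
|---|---|---|
| Chi-square, no baseline | about 0.05; 0.06 | about 0.41; 0.31 |
| Fisher exact, no baseline | about 0.02; 0.01 | about 0.29; 0.21 |
| Logistic with baseline, Wald | at or below 0.04 in both | about 0.52; 0.36 |
| Logistic with baseline, likelihood ratio | about 0.06; 0.07 | about 0.56; 0.45 |

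Repeat runs with other random seeds moved power by about 0.02. The likelihood-ratio test is mildly liberal, so part of its apparent gain is not real. The Wald test errs on the conservative side and still gains, so the gain is not an artefact of a liberal test.

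**The case against.** **The test is valid as it stands.** Randomisation protects the unadjusted comparison, and the simulated type I error of chi-square is about 5%. Chance imbalance in a prognostic variable is already covered by that error rate. This stands: the issue is efficiency, not bias.

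**Mild entrants swamp remission with noise.** A reader might infer this from the 40 to 45% figure at baseline 8. That figure assumes no true change in anyone, so it says nothing about the arm difference, and step 4 points the other way. The one-point case also applies only at exactly 8, and the documents do not say how many patients enter there. Inpatients are recruited along with outpatients, and a DSM-5 diagnosis of MDD with anxious distress is required, so such patients may be few.

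**Some patients may already be in remission at T0.** Table 1 schedules HDRS-17 at screening and at T0, and the eligibility text does not say which visit must meet the floor. A reader might infer that patients at 7 or less can start treatment. That reading rests on an omission of a kind that a condensed article may leave to the full protocol, so it is not a finding.

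**The main comparison is untouched.** The change in HDRS-17 is named as the primary outcome, and the mixed model includes baseline as a time level. This stands, and the point should not be extended to that analysis. It does not settle remission, which the abstract and the Discussion list alongside change.

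**Covariates belong in the analysis plan.** The chi-square or Fisher sentence is general and does not name remission, and an unseen plan could add a model. But the protocol does state a method for categorical variables, and that method has no baseline term.

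**The cut of 7 is a cited definition, and response is reported beside it.** This stands, and it is a reason not to replace the definition.

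**Conclusion.** The point holds as one of efficiency. The protocol's own definitions make remission depend strongly on baseline and allow remission without response from 8 to 13; this needs no outside figure. The stated test ignores baseline for an outcome that two sections place with the primary outcome, in arms of 29 with no stated stratification by severity.

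The size is a loss of about 5 to 11 percentage points of power: 0.31 unadjusted against 0.36 adjusted at an assumed baseline mean of 18, and 0.41 against 0.52 at a mean of 14. These figures rest on assumed means, SDs and effects and on complete data. The direction is more secure than the amount. The documents do not support a claim of bias towards active treatment, of an inflated error rate, or of dilution by mild entrants.

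**What to change.** In the Statistical analysis section, name remission and response at 6 weeks and analyse each by logistic regression on treatment with T0 HDRS-17 as a covariate. Fix in advance a test that is safe at this sample size: a Wald test or penalised likelihood, or instead a covariate-adjusted risk difference with robust standard errors. Only the Wald version was simulated here. Keep chi-square or Fisher as a supporting analysis.

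Optionally, as a sensitivity analysis, report remission that also meets the 50% fall from T0. Leave the cited cut of 7 or less as the definition, since changing it would lower the rates and hamper comparison with other trials.

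The abstract and the Primary outcome section should also agree on whether remission is primary.

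The cost is a few sentences and slightly more analysis; Table 1 already schedules the T0 score. There are two cautions. The likelihood-ratio version is mildly liberal with 29 per arm. A logistic odds ratio is conditional on baseline, so it does not estimate the same quantity as the crude two-by-two table; an adjusted risk difference avoids this.
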